### Secondary outcome

#### Treatment adherence

Treatment adherence will be monitored by following up with participants for three months after they start treatment. The three-month follow-up period was chosen based on feasibility and previous studies [17, 33]. Participants who begin treatment one month after the FCHVs intervention will be followed up after three months to evaluate their ongoing care. During the follow-up, participants will be asked if they are still receiving care from the same providers, if they have switched providers, or if they have stopped treatment. Participants who switched providers will be asked about the reasons for the change, while those who discontinued treatment will be asked about the reasons for their decision to stop receiving services. Participants will be asked “yes” or “no” questions: “Have you been receiving treatment for your health issues since we last met three months ago?” We will report the percentage of participants who respond “yes” to this question as an indicator of treatment adherence.

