## Methods

### Objective

The aim of this study is to analyze the active components of Gain-Life (Give informAtIoN to transform Life), a community-based intervention designed to promote help-seeking for depression care. The study will examine the effects of intervention components including information on depression, awareness of treatment options, stigma reduction, dispelling myths about depression, and sharing personal transformation experiences, on help-seeking behaviour as the primary outcome and treatment adherence as secondary outcomes. Furthermore, the study will evaluate the delivery methods and assess the feasibility, acceptability, and appropriateness of Gain-Life intervention in encouraging help-seeking for depression care.

The primary research question of this study is to determine which component of the Gain-Life intervention has a positive impact on the primary outcome of help-seeking behaviour among individuals with depression. This outcome is measured as the percentage of people seeking care from a health care provider within one month of receiving the intervention.The secondary research question aims to evaluate the intervention’s effects on different outcomes, such as treatment adherence, reduction in depression symptom severity, and the feasibility, acceptability, and appropriateness of Gain-Life in promoting help-seeking for depression treatment.

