### Symptom severity

The severity of depression symptoms will be assessed using the locally validated Patient Health Questionnaire (PHQ-9) three months after treatment initiation. The PHQ-9 is a nine-item tool commonly used to evaluate depression symptoms. Participants will rate nine common symptoms of depression based on their experiences over the previous two weeks using a 4-point scale ranging from 0 (not at all) to 3 (always) [24]. The PHQ-9 has been translated, culturally adapted, and validated in Nepal with a sensitivity of 0.94 and specificity of 0.80 for the recommended cut-off score of ≥ 10 for screening individuals with depression [42]. We will use the total scores of the PHQ-9, which range from 0 to 27, to examine the mediating effects of depression symptom severity in individuals seeking help. A higher score on the PHQ-9 indicates a more severe level of depression [24].

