### Quantitative data analysis

Quantitative data analysis will be conducted using StataIC 15.1 and MPlus (v8) [60]. Baseline characteristics of the participants (such as age, sex, caste/ethnicity, education) will be compared to assess balanced randomization. An intent-to-treat model will be used. Participants who do not receive all allocated intervention components for various reasons will be included in the intent-to-treat analysis. Despite the short three-month interval between the baseline and follow-up interviews, there is a risk of participant dropout during the follow-up period, possibly due to work-related mobility. To address this issue, we also plan to conduct the follow-up interviews via phone to minimize the risk of dropout. Any missing data or loss to follow-up will be carefully examined, and if necessary, we will utilize multiple imputation techniques to handle missing data effectively.

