### Secondary outcomes

Our secondary outcome is treatment adherence for depression care. This will be determined based on the number of participants who initiate treatment one-month post-intervention and continue to engage in care during the three-month follow-up period. General linear regression models will be used to test the secondary outcomes as well.

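### Adherence is followed up in treatment starters and tested across components with no stated denominator; read as starters-only, a component that puts more people in care can look worse

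*Protocol article*

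**What the plan says.** **Adherence, as measured.** The Treatment adherence section sets the clock at treatment start: "Treatment adherence will be monitored by following up with participants for three months after they start treatment". It then names who is followed: "Participants who begin treatment one month after the FCHVs intervention will be followed up after three months to evaluate their ongoing care". Participants are asked whether they are with the same provider, have switched or have stopped. No category exists for a person who never started. The percentage answering yes to a single question is reported "as an indicator of treatment adherence", and the section does not say a percentage of whom.

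**Adherence, as analysed.** The Secondary outcomes part of the analysis section counts the "number of participants who initiate treatment one-month post-intervention and continue to engage in care during the three-month follow-up period", again without a denominator, and adds: "General linear regression models will be used to test the secondary outcomes as well". A comparison of components is therefore planned.

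**Intention to treat.** The statements under Implementation process and Quantitative data analysis keep in the analysis those who did not receive every allocated component. They do not mention participants who never started treatment.

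**PHQ-9.** The Symptom severity section takes it "three months after treatment initiation". The Objective section lists effects to be evaluated "such as treatment adherence, reduction in depression symptom severity", and both Mediators sections use PHQ-9 as a mediator of help-seeking.

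**Anchor of the three-month visit.** It is treatment start in the Treatment adherence and Symptom severity sections, the previous meeting in the adherence question, and baseline in Quantitative data analysis ("Despite the short three-month interval between the baseline and follow-up interviews").

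**The concern.** Help-seeking within one month is the primary outcome, and the trial is sized on a component moving it from 40% to 60%. If adherence is compared only among those who started, the groups are formed after randomisation by the very event that the components aim to change. The on-level starters then include people who would not have started without the component, and the off-level has no counterpart to them. If those people persist less well, the on-level percentage falls although nobody has been made worse off.

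The results are meant to guide whether to move to a full trial or to optimise the components further. A component that increases the number in care could be marked down on adherence for that reason alone.

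**Working it through.** **Inputs from the protocol.** Help-seeking 40% (off) and 60% (on), 90% power, alpha 0.05, N = 288 in eight conditions of 36 (Sample sizes section). Each component is on in four conditions and off in four, so each level has 4 × 36 = 144.

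**The plan's own figure.** Comparing 40% with 60%, two-sided 5%, 90% power:

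- Without continuity correction: n = [1.96·√(2·0.5·0.5) + 1.2816·√(0.4·0.6 + 0.6·0.4)]² / 0.20² = 129.3, so 130 per level and 260 in total.
- With continuity correction: 140 per level, 280 in total, within 3% of 288.

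The stated size is thus consistent with an on-v-off comparison of 144 v 144 (power 92.8%, uncorrected). The sample size is not in dispute.

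**Assumptions, not in the protocol.** Starting treatment occurs at the help-seeking rates. The component deters nobody from starting and does not change retention in those who would start anyway. Let a be retention in these usual starters and b retention in the extra starters.

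**Formulas.** Extra starters as a share of on-level starters: (0.60 − 0.40)/0.60 = 1/3.

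- Starters only: off = a; on = (0.40a + 0.20b)/0.60; difference = (b − a)/3.
- All randomised, never-started counted as not in care: off = 0.40a; on = 0.40a + 0.20b; difference = 0.20b.

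The first difference is negative whenever b < a. The second is positive whenever b > 0.

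| a | b | Starters only, off v on | Difference (points) | All randomised, off v on | Difference (points) |
|---|---|---|---|---|---|
| 80% | 50% | 80% v 70% | −10 | 32% v 42% | +10 |
| 70% | 40% | 70% v 60% | −10 | 28% v 36% | +8 |
| 80% | 20% | 80% v 60% | −20 | 32% v 36% | +4 |
| 60% | 60% | 60% v 60% | 0 | 24% v 36% | +12 |

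First row in full: 0.40 × 0.80 = 0.32; 0.32 + 0.20 × 0.50 = 0.42; 0.42/0.60 = 0.70. With a from 50% to 80% and b from 20% to 60% (never above a), the starters-only difference runs from 0 to −20 points and the all-randomised difference from +4 to +12.

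**Numbers compared.** Starters: 0.40 × 144 ≈ 58 v 0.60 × 144 ≈ 86, instead of 144 v 144.

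**Sampling variation.** In 20,000 simulated trials per scenario, with a two-sided 5% test of two proportions:

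- a = 70%, b = 40%: the starters-only estimate was below zero in 89% and significantly so in 23%; the all-randomised estimate was above zero in 92% and significantly so in 31%.
- a = b = 70%: the starters-only estimate was below zero in 50% and significantly so in 2%; the all-randomised estimate was above zero in 99%.

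**PHQ-9, passages side by side.** A date counted from treatment initiation does not exist for a participant who never starts. If PHQ-9 existed only in those who sought help, help-seeking would not vary in the mediation analysis. The Symptom severity section therefore cannot stand as worded beside the Mediators sections, or beside the Objective section if symptom reduction is to be an effect of the randomised components.

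**The case against.** **The denominator is open.** A reader might infer that the protocol has settled on a starters-only comparison. It has not. The primary outcome is reported in similar terms, as a percentage of participants answering yes, and there the base is everyone. The count in the analysis section, divided by all 288, would be a valid outcome under intention to treat. This part of the objection stands. What remains is that the follow-up instruction, the clock and the answer categories are all built for starters, and that the two readings can differ in sign.

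**PHQ-9.** A reader might also infer that conditions will be compared on PHQ-9 among those who sought care. The documents do not support that. No between-condition PHQ-9 model is described. The measure is handled mainly as a mediator, and only the Objective section treats symptom reduction as an effect. The knowledge scales are given to participants at three months without restriction, and Quantitative data analysis speaks of follow-up interviews generally, which points to follow-up of everyone. The schedule figure, not shown, may settle who is seen when. Here the point is one of wording to reconcile.

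**Intention to treat.** The statements on undelivered components do not define the adherence denominator, so they neither contradict the starters-only reading nor repair it.

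**Size.** The retention rates are assumed, and 60% is the planning figure for one component only. With equal retention there is no reversal. That stands.

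**Left to the analysis plan?** A denominator often is. But the follow-up population is stated here, and it governs who is contacted. A later analysis plan cannot recover measurements that were never taken from non-starters.

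**Conclusion.** The point holds for adherence, with the limit that the denominator is unstated. Read naturally, the plan tests components within a group selected by the primary outcome. At the protocol's 40% and 60%, about one third of on-level starters would not have started without the component. That selection does not depend on the assumed retention rates, but the direction and size of the distortion do: from 0 to −20 points among starters, against +4 to +12 points among all randomised, over the range shown. Reversal is possible, not certain.

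For PHQ-9 the conclusion is narrower: the passages on its timing and use conflict and must be reconciled. The anchor of the three-month visit also differs. Treatment start and the previous meeting may nearly coincide, but baseline falls about a month or more before the one-month visit if, as usual, it precedes the intervention.

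**What to change.** 1. Define the tested secondary outcome over all 288 randomised participants: started provider care by the one-month visit and still in care at one fixed date, for example three months after that visit. Count those who had not started as not in care.
2. Report the percentage still in care among starters as descriptive only, without a test between conditions.
3. State that PHQ-9 is taken in everyone at the same fixed visit, and align the Objective, Symptom severity and Mediators sections with that.
4. Use one anchor for the three-month visit in the Treatment adherence, Symptom severity and Quantitative data analysis sections.

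**Cost.** For adherence this is wording only, because non-starters are already identified at the one-month visit. PHQ-9 in everyone needs a three-month contact with non-starters where they are not already seen for the knowledge scales; telephone follow-up is already planned. The sample size does not change.

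**Downside.** The composite overlaps with the primary outcome, since starting drives much of it, and the trial was not sized for it. It should be read as the net number kept in care, with the descriptive percentage alongside to show persistence.

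### Treatment adherence is scored from a look-back yes/no item that a participant who has stopped treatment can answer yes, although the same interview records directly who has stopped

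*Protocol article*

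**What the plan says.** The Treatment adherence section of the protocol article gives the purpose of the follow-up: those who have begun treatment "will be followed up after three months to evaluate their ongoing care". At that interview, "participants will be asked if they are still receiving care from the same providers, if they have switched providers, or if they have stopped treatment". Switchers are asked why they changed, and "those who discontinued treatment will be asked about the reasons for their decision to stop receiving services".

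The section then scores the outcome from a different item, the yes/no question "Have you been receiving treatment for your health issues since we last met three months ago". The article will report the percentage answering yes "to this question as an indicator of treatment adherence". It gives no other scoring rule there.

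Under Quantitative data analysis, the Secondary outcomes section says the outcome rests on "the number of participants who initiate treatment one-month post-intervention and continue to engage in care during the three-month follow-up period".

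**The concern.** The purpose and the analysis definition both describe persistence: a person starts care and remains in it. The scored item asks about receipt of treatment over a past interval. It contains no word such as still or currently, and nothing in the scoring rule removes people who have since stopped.

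The trial is meant to help choose which components to keep. If stoppers are counted as adherent, a component that keeps people in care becomes harder to tell from one that prompts only a few early visits. The possible error lies mainly on one side. Stoppers may answer yes, whereas people still in care have little reason to answer no.

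**Working it through.** **Step 1: the passages side by side.** Take a participant who started treatment by the one-month visit, attended a few more times, and had stopped before the follow-up interview.

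| Source in the article | Result for this participant |
|---|---|
| Three-way status question (Treatment adherence) | Stopped |
| Yes/no item (Treatment adherence) | Yes is a truthful answer; no is also defensible |
| Scoring rule (Treatment adherence) | Adherent, if the answer is yes |
| Definition (Secondary outcomes, analysis section) | Not adherent, because care did not continue |

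One interview can therefore yield a record of stopped and a score of adherent. The article has no rule for which prevails.

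**Step 2: is there a stated figure to reproduce?** There is none for adherence: no expected rate, sample size or power. The 288 in the sample size section was set for help-seeking (40% against 60%), and nothing here depends on it.

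**Step 3: illustration of the size.** All inputs in this step are assumptions.
- c is the true share of starters still in care: c₁ = 0.60 with a component, c₀ = 0.40 without. These values equal the article's planning rates for help-seeking, but they are not adherence data.
- q is the share of stoppers who answer yes, taken as equal in all conditions.
- Everyone still in care answers yes.

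Scored rate: S = c + (1 − c)q.

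Scored difference: S₁ − S₀ = (c₁ − c₀)(1 − q).

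| q | S₀ | S₁ | Difference |
|---|---|---|---|
| 0 | 0.40 | 0.60 | 20 points |
| 0.25 | 0.40 + 0.60 × 0.25 = 0.55 | 0.60 + 0.40 × 0.25 = 0.70 | 15 points |
| 0.50 | 0.40 + 0.60 × 0.50 = 0.70 | 0.60 + 0.40 × 0.50 = 0.80 | 10 points |
| 0.75 | 0.40 + 0.60 × 0.75 = 0.85 | 0.60 + 0.40 × 0.75 = 0.90 | 5 points |

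As a further assumption, suppose half of the 288 start treatment, so 72 at each level of a factor. A two-sided 5% comparison of two proportions (normal approximation, pooled variance under the null) then has power of about 67% at q = 0, and 46%, 28% and 15% at q = 0.25, 0.50 and 0.75.

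**Step 4: how far the equal-q assumption matters.** If q differs between levels, the scored difference is (c₁ − c₀) + (1 − c₁)q₁ − (1 − c₀)q₀. With q₁ = 0.50 and q₀ = 0 it is 0.20 + 0.20 − 0 = 40 points. With q₁ = 0 and q₀ = 0.50 it is 0.20 + 0 − 0.30 = −10 points. Shrinkage is therefore the result under equal misreporting. It is not guaranteed.

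**The case against.** The best defence is that the two sections work together. The adherence section calls the yes/no item only an indicator. The analysis section could be read as fixing the analysed outcome, with the three-way question supplying it. The wording of the item can also be heard as implying care throughout the interval. Only the English is shown, while participants need to be proficient in Nepali, and someone asked in the same interview whether they have stopped may be less likely to give an inconsistent yes. These points stand to this extent: the item is ambiguous, it is not shown to measure any treatment at all, and the rate of misclassification is unknown. They do not remove the mismatch. The article names the item and the percentage to be reported, and gives no rule for a yes from someone recorded as stopped.

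Three stronger readings are tempting, and the article does not support them.

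- *Persistence is not measured.* It is. The three-way question asks about it directly. The problem is which item is scored.
- *People who first start treatment after the one-month visit would be counted as adherent.* Both sections already confine the outcome to those starting treatment around one month after the intervention, so late starters fall outside it whatever they answer.
- *The three-month recall phrase contradicts the visit schedule.* A reader might infer this from the remark on dropout in the quantitative analysis section, "Despite the short three-month interval between the baseline and follow-up interviews". But the adherence section says "Treatment adherence will be monitored by following up with participants for three months after they start treatment". On that timing, a previous meeting about three months earlier fits the question. The conflict arises only if the passing remark sets the date of the adherence visit.

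It is also fair to say that the three-way status is not a perfect measure. It describes the situation at follow-up, so a person who lapsed and came back counts as continuing.

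**Conclusion.** The point holds as a mismatch between a stated scoring rule and the article's own definition of the same outcome. It is not a detail left to an analysis plan, because the article itself fixes the item and the percentage to be reported.

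Its size cannot be established from the documents. The loss of 5, 10 or 15 of 20 points, and the matching fall in power, depends on the assumed continuation rates, the assumed number of starters and equal misreporting in all conditions. These figures show how the error would act and are not a forecast.

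The reach is limited to the secondary outcome. It should be corrected before that outcome is analysed.

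**What to change.** Define adherence from the three-way status question, among participants who had started treatment by the one-month visit:

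- still receiving care from the same provider: continuing;
- switched to another health care provider: continuing, with health care provider meaning what it means for the primary outcome;
- stopped: not continuing.

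State how a switch to someone outside that definition, such as a traditional healer, is scored. Keep the yes/no item as a descriptive result, and use the same definition in the outcome and analysis sections.

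The cost is mainly a change of wording in the outcome definition, since the status question is already asked. The article mentions asking switchers for their reasons. If the type of the new provider is not also recorded, one field has to be added. Data collection began in July 2024, so the change should be dated and recorded before anyone analyses adherence by condition. The reported adherence rate will probably be lower, and the report should say that status at follow-up does not capture temporary lapses.

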### Mediators

We will examine the mediating effects on help-seeking behaviour at the three-month follow-up. The mediating variables include knowledge, attitude, and perception of depression, as well as the severity of depressive symptoms. These mediating variables were selected based on the impact of these knowledge, attitude, and perception of depression on help-seeking [10, 11, 29, 69].

### Knowledge, attitudes, perceptions of depression and available services

Participants’ knowledge, attitudes, and perceptions regarding depression and available services will be assessed during a three-month follow-up. Three structured questionnaires, each with four response options, have been developed based on the intervention content. The knowledge about depression scale consists of 7 items, the stigma and myths scale consists of 5 items, and the knowledge about available services scale consists of 8 items. These scales will be asked during the three-month follow-up, not at baseline. Each question will have one correct response and three incorrect responses. Participants will choose the correct response for each question after a research assistant reads the question and all possible responses. Composite scores will be calculated based on the number of correct responses for each scale for analysis. We will report the number of correct responses in each domain: knowledge, attitudes, and perceptions on depression. Additionally, we will also use continuous scores (i.e. total score of each domain) when performing mediator analysis.

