## Outcome measures

### Primary outcome

#### Help-seeking behaviour

Changes in help-seeking behaviour will be assessed by determining if participants sought mental health treatment within one month after attending the FCHVs intervention. Mental health treatment is defined as treatment provided by health care providers including trained primary health care workers, doctors, and mental health specialists. This does not include treatment provided by traditional healers and religious leaders. Research assistants, who are unaware of the participants’ assignment to the intervention, will visit their homes one month post-intervention. They will inquire about the participants’ interactions with FCHVs, the places/providers they visited for seeking care, and the reasons for choosing a specific provider using a semi-structured questionnaire. We will not verify the accuracy of the treatment they received. Participants who did not seek treatment will also be asked about the reasons for not seeking care and their plans to seek treatment soon. Participants will be asked a “yes” or “no” question: “Did you seek help for your health issue after attending the FCHV session?” with a yes or no response. We will report the percentage of participants who respond “yes” to this question as an indicator of seeking treatment.

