### Mediators

Previous studies have demonstrated a positive correlation between mental health literacy, attitudes, stigma, and symptom severity in relation to help-seeking behaviour [10, 11, 29, 69]. Our formative study also indicated that individuals who were familiar with depression symptoms and aware of mental health service providers and locations were more inclined to seek help from health care providers. Therefore, we aim to investigate whether participants’ knowledge, attitudes, and stigma can act as mediators in influencing help-seeking behaviour. Furthermore, we will also assess the symptom severity of depression, as measured by the PHQ-9 at a three-month follow-up, to determine if it plays a mediating role in help-seeking behaviour. We will use the Baron and Kenny method along with a path analysis to examine the mediation effects. For the Baron and Kenny method, a series of general linear regression models will be tested to assess mediation [49]. Mplus will be used to conduct a path analysis looking at the direct and indirect effects to determine if the hypothesized mediator is in fact a mediator in the relationship between the predictor variable and outcome of interest [19].

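### Knowledge, stigma, services and PHQ-9 scores are tested as mediators of help-seeking but measured after it, so the mediation analysis cannot establish direction

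*Protocol article*

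**What the plan says.** **Outcome.** Under Help-seeking behaviour, the primary outcome is assessed by "determining if participants sought mental health treatment within one month after attending the FCHVs intervention". Blinded research assistants "will visit their homes one month post-intervention" to record it. The Objective section uses the same one-month window.

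**Scales.** Three questionnaires cover knowledge of depression (7 items), stigma and myths (5 items) and available services (8 items). Their timing is explicit: "These scales will be asked during the three-month follow-up, not at baseline".

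**PHQ-9.** The Symptom severity section states: "The severity of depression symptoms will be assessed using the locally validated Patient Health Questionnaire (PHQ-9) three months after treatment initiation". It describes the score's mediating role as one among people who seek help. The Mediators section of the analysis plan instead says: "we will also assess the symptom severity of depression, as measured by the PHQ-9 at a three-month follow-up".

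**Analysis.** The Mediators section under Outcome measures states: "We will examine the mediating effects on help-seeking behaviour at the three-month follow-up". The analysis section names a series of Baron and Kenny regressions and a path analysis of direct and indirect effects in Mplus. Neither the mediation sections nor the limitations in the Discussion mention the order of measurement.

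**The concern.** A mediator has to come before the outcome that it explains. Here the written order is component, then help-seeking (by month one), then mediator score (month three). By month three, a participant who saw a provider may have learned from that contact what the scales test, and may have been treated. Randomisation protects the path from component to score. It does not protect the path from score to help-seeking, and there is no earlier score to adjust for.

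At stake is the explanation of how the components work. A care-to-knowledge effect could be published as evidence that better knowledge or lower stigma brought people into care.

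**Working it through.** **1. The plan's own figure.** The article gives no figure for the mediation analysis. Its one reproducible figure is the sample size of 288, for 40% against 60% at 90% power and 0.05 significance. For a main effect (half against half), the two-sided calculation gives 130 per level (260 in total), or 140 per level (280) with continuity correction. The latter is within 3% of 288, and 144 per level gives power of about 0.93. This figure is not in question; only the 40% and 60% are used below.

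**2. Time order.**

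| Variable | When measured |
|---|---|
| Help-seeking | Counted within one month, recorded at one month |
| Three scales | Three-month follow-up only |
| PHQ-9 (Symptom severity) | Three months after treatment starts |
| PHQ-9 (analysis, Mediators) | A three-month follow-up |

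The scales follow the outcome by about two months. The gap is nearer three months if follow-up runs from the one-month visit, as the wording of the adherence question suggests.

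**3. Size of the false mediated share.** Let X be a component (off/on, equal halves) and Y be help-seeking, with probability 0.4 or 0.6. Y then has variance 0.24 within each level. Let the later score be M = dY + cX + e, where e has SD 1. M has no effect on Y, so true mediation is zero. The values of d (shift due to care) and c (shift due to the component) are assumptions.

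- Component to score: a = 0.2d + c
- Score to help-seeking, given X: b = 0.24d / (1 + 0.24d²)
- Apparent mediated share: ab / 0.2

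With c = 0 the share is 0.24d² / (1 + 0.24d²):

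| d (SD) | Share |
|---|---|
| 0.2 | 0.0096 / 1.0096 = 1.0% |
| 0.5 | 0.06 / 1.06 = 5.7% |
| 0.8 | 0.1536 / 1.1536 = 13.3% |
| 1.0 | 0.24 / 1.24 = 19.4% |

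The scales were written from the intervention content, so a direct component effect on them is plausible. With c = 0.5 and d = 0.5, a = 0.6 and b = 0.12 / 1.06 = 0.113. The share is 0.6 × 0.113 / 0.2 = 34%.

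**4. How often mediation would be declared.** This used 4,000 simulated trials of 288 participants per setting, with linear regressions and both paths required to be significant at 5%. There is no true mediation in any setting.

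| Component effect on score | d = 0 | d = 0.25 | d = 0.5 | d = 0.8 |
|---|---|---|---|---|
| None | 0.2% | 4% | 13% | 25% |
| 0.5 SD | 5% | 54% | 98% | not run |

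**5. PHQ-9.** People who never start treatment have no date from which to count three months. If the PHQ-9 is taken only in starters, help-seeking does not vary among those measured and the model cannot be fitted. If it is taken in everyone, it can reflect response to care.

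**6. Would measuring at one month cure it?** Suppose the scales move to the one-month visit and the outcome becomes being in care at three months. Let the probability of being in care be p₁ for month-one seekers and p₀ for the others. The total effect becomes 0.2(p₁ − p₀), and b is also multiplied by (p₁ − p₀). The factor cancels, so for the same d and c the share is that of step 3. Month-one care still drives both score and outcome.

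**The case against.** **Mediation could mean help-seeking at three months.** The sentence in the Mediators section allows that reading. However, the only three-month care item described is the adherence question. Score and outcome would then be measured together with no baseline score, so direction would still be unknown.

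**The PHQ-9 may not be timed from treatment start.** A reader might infer from Symptom severity that it is. The article does not support that as a flat statement, because the analysis section gives a different timing and the schedule figure is not available here. What stands is an inconsistency. The claim that the model cannot be fitted applies only if the score is taken in starters alone.

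**The magnitudes are assumed.** This is correct. The article gives no effect of care on the scales, and a small effect (0.2 SD) makes the false share about 1%. The size is uncertain, but the lack of time order is not.

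**The analysis plan could deal with it.** It could change how the results are described. It could not supply a score that was never taken before the outcome.

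**Only a supporting analysis is affected.** This stands, and it limits the severity.

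**Conclusion.** The concern holds for the mediation analysis. As scheduled, it cannot distinguish a cause of help-seeking from a consequence of it. Under the assumed effects, with no true mediation, the spurious share runs from about 1% to 19% when the component does not itself move the score. It is about 34% in the one combined case worked above. These figures assume linear models, the 40% and 60% planning rates and equal halves.

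A reader might infer that mediation results will decide which components are kept. The article does not say so. Its primary question is which component affects help-seeking, that question is answered by main effects, and the Discussion says only that the results will guide next steps. The component effects on help-seeking, the adherence analysis and the sample size are untouched. This is a lower-severity correction to a supporting analysis.

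**What to change.** 1. **PHQ-9.** Remove it as a mediator of help-seeking and analyse it as an outcome. The secondary research question already lists reduction in symptom severity. Reconcile the two statements of when it is taken, and state in whom. This needs no new data if the score is already collected in everyone.
2. **Three-month scales.** Report component effects on knowledge, stigma and services scores, which randomisation supports. Report the relation of these scores to help-seeking as an association, without the word mediation. This costs nothing and suits participants already enrolled.
3. **Mediation claim.** Keep it only if the scales can be given before help-seeking is counted, for example straight after the last session. Participants who began care between sessions, which the implementation section foresees, need to be identified. The cost is 20 items at an extra point. Reading them to everyone may expose participants to content that their condition withholds. Because baseline collection began in July 2024, the change may also split the sample between two schedules.
4. **One-month alternative.** Moving the scales to the one-month visit with a three-month in-care outcome is not enough by itself. It would also need adjustment for month-one help-seeking, or restriction on it.
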